## Abstract

**Background:**

Major depressive disorder (MDD) and generalized anxiety disorder (GAD) are highly prevalent among university students and predict impaired college performance and later life role functioning. Yet most students do not receive treatment, especially in low-middle-income countries (LMICs). We aim to evaluate the effects of expanding treatment using scalable and inexpensive Internet-delivered transdiagnostic cognitive behavioral therapy (iCBT) among college students with symptoms of MDD and/or GAD in two LMICs in Latin America (Colombia and Mexico) and to investigate the feasibility of creating a precision treatment rule (PTR) to predict for whom iCBT is most effective.

**Methods:**

We will first carry out a multi-site randomized pragmatic clinical trial (*N* = 1500) of students seeking treatment at student mental health clinics in participating universities or responding to an email offering services. Students on wait lists for clinic services will be randomized to unguided iCBT (33%), guided iCBT (33%), and treatment as usual (TAU) (33%). iCBT will be provided immediately whereas TAU will be whenever a clinic appointment is available. Short-term aggregate effects will be assessed at 90 days and longer-term effects 12 months after randomization. We will use ensemble machine learning to predict heterogeneity of treatment effects of unguided versus guided iCBT versus TAU and develop a precision treatment rule (PTR) to optimize individual student outcome. We will then conduct a second and third trial with separate samples (*n* = 500 per arm), but with unequal allocation across two arms: 25% will be assigned to the treatment determined to yield optimal outcomes based on the PTR developed in the first trial (PTR for optimal short-term outcomes for Trial 2 and 12-month outcomes for Trial 3), whereas the remaining 75% will be assigned with equal allocation across all three treatment arms.

**Discussion:**

By collecting comprehensive baseline characteristics to evaluate heterogeneity of treatment effects, we will provide valuable and innovative information to optimize treatment effects and guide university mental health treatment planning. Such an effort could have enormous public-health implications for the region by increasing the reach of treatment, decreasing unmet need and clinic wait times, and serving as a model of evidence-based intervention planning and implementation.

**Trial status:**

IRB Approval of Protocol Version 1.0; June 3, 2020. Recruitment began on March 1, 2021. Recruitment is tentatively scheduled to be completed on May 30, 2024.

**Trial registration:**

ClinicalTrials.govNCT04780542. First submission date: February 28, 2021.

## Administrative information

Note: the numbers in curly brackets in this protocol refer to SPIRIT checklist item numbers. The order of the items has been modified to group similar items (see http://www.equator-network.org/reporting-guidelines/spirit-2013-statement-defining-standard-protocol-items-for-clinical-trials/).

## Introduction

### Background and rationale {6a}

The World Mental Health (WMH) community surveys [1] across 21 countries (including Colombia and Mexico) documented high prevalence, unmet need for treatment, and associated college attrition due to common mental disorders (CMDs) among university students. As a result, WMH launched the WMH-International College Student (ICS) initiative to implement inexpensive Internet-based needs assessment surveys to help evaluate the treatment gap and barriers to obtaining treatment of CMDs [2]. WMH-ICS surveys have so far been carried out in 15 mostly high-income countries and are planned for other countries. These surveys confirm the high prevalence [3], impairment [4], and unmet need for treatment [5] of CMDs among college students, especially in low- and middle-income countries (LMICs), where only 10–20% of students with CMDs receive any treatment [6–8]. Importantly, the proportion of young people in LMICs who attend college is small and these students have particular needs [9], as the rapid growth of tertiary education in these countries means that many are first-generation college students [10, 11] who have low socialization into the challenges of college life, high financial stress, and in many cases high pressures to succeed to help support their extended families [12, 13]. These special challenges create high levels of emotional problems [14, 15] that often interfere with academic success [16, 17]. However, institutions of higher education in LMICs, despite the important public investment in these students’ higher education, are not well-equipped to deal with these problems due to their low staff-to-student ratios and low resources to manage student CMDs [11, 18]. We seek to evaluate and optimize the effectiveness of low-cost self-guided and supporter-guided Internet-delivered transdiagnostic cognitive behavioral therapy (iCBT) to provide a feasible way to address the enormous unmet need for treatment in this critical segment of the LMIC population [9].

Internet-delivered interventions may be particularly well suited for college students as they address many barriers to treatment in this population, such as scheduling and transportation, cost, and stigma while fostering a sense of control. Whereas Internet-delivered interventions are becoming increasingly common in the USA and Europe [19], they remain under-utilized in LMICs [20, 21] in general and in Latin America in particular [22]. Importantly, existing research on Internet interventions in LMICs shows that such interventions are feasible and at least as effective as they are in high-income countries [20–22]. Literacy and Internet access, which limit Internet interventions in the general population of many LMICs, are not obstacles among college students, most of whom have email addresses (often provided by their universities), smart phones, and access to computers with Internet access.

Five project innovations are noteworthy. First, few controlled trials of Internet-based interventions have been implemented for CMDs in LMICs [20–22]. Our study is innovative in using iCBT to treat LMIC university students. iCBT has been widely used among college students in high-income countries with multiple meta-analyses attesting to its effectiveness [23, 24]. A recent meta-analysis of the effectiveness of digital interventions for mental health in LMICs [21] found that only one country in Latin-America, Colombia, implemented an iCBT study among university students. That study’s outcomes support the potential of using iCBT for university students in Latin American countries [25].

Second, the iCBT program we plan to use, *SilverCloud* (see below), is a transdiagnostic program [26, 27] focused on treatment of mood and anxiety disorders, either with or without a number of other comorbid disorders (such as eating disorders, insomnia, or substance use disorders). This is important because WMH-ICS data show that comorbidity is highly prevalent among LMIC college students [3] and strongly predicts role impairment [4]. Evaluation of transdiagnostic interventions is a high-priority National Institute of Mental Health research area (NIMH Strategic Objective 3.1) [28].

Third, while most trials evaluate aggregate effects of treatment, growing evidence suggests heterogeneity of treatment effects (HTE) such that different types of people benefit from different types of treatment [29]. Machine learning can use a large number of baseline characteristics to estimate a prediction model for each treatment arm, use counter-factual logic to assign predicted outcome scores to each student for each treatment, and examine individual difference scores to decide which treatment is best for each student. This information could be very useful for deciding what type of treatment to offer different types of students. Therefore, following an initial pragmatic clinical trial from which we will develop a precision treatment algorithm based on machine learning, we will attempt to evaluate the implications of using that rule in a second and third trial carried out in subsequent years to evaluate the extent to which the PTR would improve on randomization.

Fourth, we will investigate barriers to seeking treatment by carrying out a needs assessment survey in parallel with the intervention and examining patterns and correlates of barriers to seeking treatment. Students who are identified in the needs assessment survey as meeting the same depression and anxiety criteria as specified for the main trial but who do not seek treatment at the clinic will be offered the opportunity to participate in the trial. Depending on information obtained about barriers to treatment, the outreach efforts to recruit these students might change over the course of the trial. If so, information about variation in these efforts will be included in developing the PTR. With this ancillary trial, we will evaluate the extent to which iCBT, by providing a confidential and convenient way of obtaining treatment, can increase the proportion of students with CMDs who seek treatment. This is important because the proportion of students with CMDs who seek treatment currently is quite low. Several other interventions like this could easily be envisioned, such as campus-wide interventions to increase awareness of mental health clinics and reduce stigma [30]. However, universities are understandably reluctant to implement such interventions and it would be unethical to do so prior to having access to and evidence for the effectiveness of scalable interventions, like guided or un-guided iCBT. Based on this practical and ethical reality, we believe that a good first step in investigating opportunities for expanding treatment is the one proposed here and that the infrastructure created by this project can subsequently be used to facilitate implementation and evaluation of other outreach interventions aimed at addressing the problem of unmet need for treatment.

Fifth, we will use an innovative ensemble machine learning precision treatment modeling method [31] to develop the PTR. In addition to using an innovative modeling approach, we will include a much more extensive set of prescriptive predictors (*i.e., predictors of individual differences in the effects of CBT compared either to no treatment or other types of treatment* [32]) in the baseline assessment than in prior efforts to develop a PTR for CMD treatment. Prior studies typically examined only a handful of prescriptive predictors [33]. The prescriptive predictors we use will include all those found consistently in prior studies [32].

Given the current situation of the global coronavirus disease 2019 (COVID-19) pandemic, there is a growing need and growing acceptance of interventions delivered at a distance. This trial is timely with the potential to provide valuable knowledge and tools to meet these challenges. Moreover, the implications for treatment delivery will extend well beyond the circumstances (e.g., confinement) caused by the current pandemic.

## Objectives {7}

The overall goals of this study are to evaluate the effects of expanding treatment of CMDs among college students with symptoms of major depressive disorder (MDD) and/or generalized anxiety disorder (GAD) in two LMICs in Latin America (Colombia and Mexico) and to investigate the extent to which treatment outcomes could be improved by creating precision treatment algorithms to predict which intervention would be best for which students. The intervention will be a scalable and inexpensive intervention: iCBT. We have four specific objectives.

Objective 1: To carry out a year 1 pragmatic clinical trial with students in participating universities in Colombia and Mexico. Students will be recruited both from student mental health clinic waiting lists and from outreach emails sent to probability samples of other students. The student clinics have long waiting lists for all but the most urgent cases. Students on wait lists will be offered a two-thirds chance to receive iCBT immediately while staying on the list. The same offer will be made to students from the general student body recruited from emails. Interested students will be required to complete a baseline self-report assessment and, if eligible, to be randomized with equal allocation either to unguided iCBT (33%), guided iCBT (33%), or treatment as usual (TAU; that is, they will remain on the clinic waiting list until their appointment). Short-term aggregate intervention effects among students randomized across arms will be assessed 90 days after randomization and longer-term effects 12 months after randomization.

Objective 2: To use ensemble machine learning methods to predict heterogeneity of treatment effects of unguided iCBT versus guided iCBT versus TAU and develop a PTR to predict which students will respond best to which intervention. We will build a PTR for 90-day remission and a separate PTR for 12-month remission based on the year 1 pragmatic trial.

Objective 3: To carry out two additional trials in years 2 and 3 that build on the results of the first trial. Recruitment will be the same as in the first trial but randomization will be different in that a random 25% of participants will be randomized to the treatment estimated by the PTR for short-term response (the year 2 trial) or 12-month remission (the year 3 trial) based on the year 1 trial and the remaining 75% will be randomized with equal allocation across all 3 treatments.

Objective 4: The technology for delivering iCBT, developing and updating PTRs, and carrying out Internet-based mental health needs assessment surveys will be disseminated to colleges and universities in LMICs throughout Latin America. This dissemination will occur through conferences, seminars, and responding to requests for consultation.

## Trial design {8}

First, we will conduct a three-arm single-blind parallel assignment individually randomized equal allocation controlled pragmatic trial on *n* = 1500 students. It will compare aggregate effects of unguided iCBT, guided iCBT, and TAU at 90 days and 12 months. Consistent with previous research, we hypothesize that guided iCBT will have superior aggregate treatment effects to unguided iCBT, but as this will be an initial study that combines novel treatments, methods of treatment delivery, and new ways of matching treatments to students, we were not able to draw on prior theory or research to hypothesize whether the aggregate treatment effects of iCBT will be superior to those of TAU. However, we hypothesize that comparative effectiveness across the three arms will vary significantly by student baseline socio-demographic, environmental, and clinical characteristics,

This initial trial will be followed by two additional trials using the same recruitment methods and same interventions but differing in allocation rules. In the second trial, 25% of n = 1000 students will be individually assigned to the treatment estimated by the PTR in the first trial to yield an optimal short-term response for the student, with the remaining 75% randomized with equal allocation across all 3 treatments. In the third trial, 25% of n = 1000 students will be individually assigned to the treatment estimated by the PTR in the first trial to yield an optimal 12-month probability of remission for the student, with the remaining 75% randomized with equal allocation across all 3 treatments. We hypothesize that students assigned to the treatment recommended by the PTRs will have significantly better outcomes than those randomized across types of treatment. These additional trials will provide a direct evaluation of the value of the PTRs.

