#### Expected effect size and power calculations

We powered the study to estimate heterogeneity of treatment effects as defined by the increase in the proportion of patients we would expect to remit from the primary outcomes based on optimized rather than randomized treatment of 5%. We considered this the minimum difference of interest. Although we will be interested both in continuous (i.e., differences in mean scores on symptom rating scales) and categorical (i.e., probabilities of treatment response and remission) outcomes, we evaluated statistical power for a categorical measure of episode remission because this is of greatest clinical importance and because larger samples are required for powerful detection of effects on categorical than continuous outcomes. Meta-analyses of previous iCBT trials for CMDs show that treatment response is approximately 50% and remission is approximately 30%, with rates roughly half these values for control conditions. Closed-form solutions show that samples with fewer than 150 patients per arm provide adequate statistical power (.8 power based on .05-level two-sided tests) to detect effect sizes this large even after making reasonable adjustments for loss to follow-up. However, estimating power to detect heterogeneity of treatment effects is more complex because closed-form solutions do not exist and simulation is needed to determine required sample sizes.

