We carried out such a simulation by building a series of hypothetical population models that assumed that each patient was randomized either to iCBT or a control condition; that the aggregate remission rates after adjusting for loss to follow-up were 27.5% and 17.5% in the two treatment arms, respectively; and that a series of relatively complex nonlinear-interactive multivariate associations existed between 20 predictors and remission. The assumed distributions of predictors and interaction values among predictors were consistent with those found in previous studies. We varied these coefficient values in different models to maintain the same aggregate remission rates but to have the difference between remission rates based on randomized versus optimized treatment vary between 0 and 15%. In each model, the remission rate if intervention assignment was randomized was set at 10% (i.e., 27.5–17.5%), but the remission rate if intervention assignment was optimized (i.e., if each student who would have a better outcome if assigned to iCBT was, in fact, assigned to iCBT and all other students were assigned to the control condition, which in some cases could involve these students receiving treatment at the student clinic and having better outcomes than if they received iCBT) was varied between 0 and 15%. We used a state-of-the-art ensemble machine learning method detailed in the proposal to estimate heterogeneity of treatment response. We discovered that adequate statistical power (again defined as .8 power based on .05-level two-sided tests) to detect a difference between the two remission rates of 5%, which we considered the minimum difference of interest, would require a sample of at least 500 patients per treatment arm [59]. A difference of 5% would represent a 50% increase on the 10% aggregate base of the difference in the remission rate between intervention and control groups. Based on a review of previous precision treatment analyses of CMDs, a difference of this magnitude is plausible. Based on this result, we designed the study to have a sample size of 500 per treatment arm. As noted above in the discussion of the sample design, we will have 1500 eligible students to randomize across three arms in the first trial, making it possible for us to estimate a precision treatment model based on data obtained in this trial. However, as noted above in the section on study design, the 12-month follow-up data for these students will not be available until YR2 and it will be possible to use the results of the model for the trial 2 randomization for the first time in YR3. We will replicate the model with follow-up data for students randomized in YR2 and use the harmonized precision treatment model results obtained in YR3 for a final Trial in YR4.

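### Trials 2 and 3: the stated comparison of 250 PTR-assigned with 750 randomized students has about 33–37% power for the 5-point minimum difference, no power is given for it, and the abstract's 500 per arm contradicts it

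*Protocol article*

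**What the plan says.** - **Hypothesis for Trials 2 and 3** (Trial design {8}): "We hypothesize that students assigned to the treatment recommended by the PTRs will have significantly better outcomes than those randomized across types of treatment". The section presents these trials as the direct evaluation of the PTRs.
- **Allocation** (Trial design {8}): in each later trial, "25% of n = 1000 students will be individually assigned to the treatment estimated by the PTR in the first trial". The other 75% are randomized equally over the three treatments. This gives 250 and 750, and Sample size {14} confirms 1000 per later trial.
- **Abstract, Methods:** the later trials have 500 per arm, "but with unequal allocation across two arms: 25% will be assigned to the treatment determined to yield optimal outcomes".
- **Target difference** (Expected effect size and power calculations): the study is powered for "the increase in the proportion of patients we would expect to remit from the primary outcomes based on optimized rather than randomized treatment of 5" percentage points. The criterion is "adequate statistical power (again defined as .8 power based on .05-level two-sided tests", applied "to detect a difference between the two remission rates of 5%, which we considered the minimum difference of interest".
- **Result of the simulation** (same section): that power "would require a sample of at least 500 patients per treatment arm". The text uses this figure to justify estimating the precision model from Trial 1. It gives no power for Trials 2 and 3.
- **Rates assumed** (same section): "the aggregate remission rates after adjusting for loss to follow-up were 27.5% and 17.5% in the two treatment arms, respectively", from a model with one iCBT arm and one control arm.

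**The concern.** The later trials are the only test of the PTR in students who did not contribute to building it. The article gives a group hypothesis for them and a minimum difference for the study as a whole, but never checks one against the other. The group assigned by the rule is only a quarter of each trial, and the abstract's per-arm figure hides this.

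Two things are at stake. A rule that delivers the 5-point gain could still fail to show it in a simple comparison of the two groups. That comparison also leaves information unused: about one third of the 750 randomized students (some 250) receive their recommended treatment by chance, and their outcomes could help to estimate the value of the rule. This chance overlap is not a bias, because it is part of what optimized versus randomized means and is already inside the 5 points. The issue is precision.

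**Working it through.** **Inputs from the article.** Two-sided 0.05, power 0.80, gain of 5 points, 1000 students per later trial split 25%/75%, remission 27.5% (iCBT) and 17.5% (control).

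**Randomized mean.**
- Two-arm model: (27.5 + 17.5)/2 = 22.5%.
- Three arms, assuming both iCBT arms are at 27.5%: (27.5 + 27.5 + 17.5)/3 = 24.2%.

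**The plan's own figures.** The closed-form statement of fewer than 150 per arm for the aggregate effect is reproduced: 30% v 15% needs 121 per arm, or 143 with an assumed 15% dropout. The 500 per treatment arm comes from a simulation whose population models are not given, so it cannot be reproduced. It is not a two-group figure: a direct 500 v 500 test of 5 points has only 43–45% power and would need 1177–1227 per group.

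**Power of 250 v 750.** At 22.5% v 27.5%, unpooled:
- SE = √(0.275×0.725/250 + 0.225×0.775/750) = √(0.0007975 + 0.0002325) = 0.0321
- z = 0.05/0.0321 = 1.56; power = Φ(1.56 − 1.96) = 34%
- Detectable difference at 80% power: (1.96 + 0.84) × 3.21 ≈ 9 points

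A pooled test gives 37% and a 40,000-run simulation 36%. At 24.2% v 29.2% the three figures are 33%, 35% and 35%. Base rates from 17.5% to 30% give 30–42%. At 1:3 allocation, 80% power would need about 3100–3230 students per trial.

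**Using all 1000 students.** Whatever arm the PTR recommends, a student's chance of receiving it is 0.25 + 0.75/3 = 1/2, and of each other arm 0.75/3 = 1/4. Whether a student is concordant with the PTR is therefore itself randomized.
- Randomized mean = (1/3) × concordant mean + (2/3) × discordant mean.
- So PTR minus balanced randomization = (2/3) × (concordant mean − discordant mean). A 5-point gain corresponds to a 7.5-point concordance contrast.
- At 22.5%: concordant 27.5%, discordant 20.0%, about 500 each.
- SE = (2/3) × √(0.275×0.725/500 + 0.20×0.80/500) = (2/3) × 0.0268 = 0.0179
- z = 0.05/0.0179 = 2.80; power = Φ(2.80 − 1.96) = 80%
- Variance ratio against 250 v 750: (3.21/1.79)² ≈ 3.2

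| Randomized mean | 250 v 750 | All 1000, by concordance |
|---|---|---|
| 22.5% | 34–37% | 79–80% |
| 24.2% | 33–35% | 78% |

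The simulated type I error of the concordance test is 0.049–0.050.

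**Sensitivity, at the 22.5% base, unpooled.**
- Analysed numbers cut by a further 30% (an assumption): SEs rise by 1/√0.7, giving about 26% and 65%.
- The estimated PTR attains only 4 points (an assumption): optimized 26.5%, discordant 26.5 − 6.0 = 20.5%. For 250 v 750, z = 0.04/0.0318 = 1.26, power 24%. For all 1000, z = 0.04/0.0178 = 2.24, power 61%.

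**The case against.** The strongest reply is that the article states a hypothesis for Trials 2 and 3, not a test. It names no estimator, outcome scale or analysis set for them, and an analysis plan that is not shown may do so. The section on heterogeneity of treatment effects already names a targeted estimator of best-predicted treatment against balanced randomization. It does not say that this applies to the later trials, but an analysis of all students would be within the declared methods.

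That much stands: 250 v 750 is read from the stated hypothesis and allocation, not from a specified test. It does not dispose of the point. The article itself fixes the groups, the numbers and the minimum difference, and these do not fit together. The abstract's per-arm figure is wrong on any reading.

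Other limits also stand:

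- A reader might infer that the article claims 80% power for 250 v 750, or that Trials 2 and 3 were designed to detect 5 points. It does not say so: the simulation is tied to Trial 1, and the broad statement that the study was powered for 5 points is not carried over to the later trials.
- A reader might infer that the later trials will probably be negative on every outcome. The figures cover binary remission without covariate adjustment. The primary outcomes are also analysed as scores, and the article itself notes that categorical outcomes need larger samples.
- The rates come from a two-arm model and are described as already adjusted for loss to follow-up. A further 30% loss is purely illustrative and may count loss twice.

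**Conclusion.** The point holds in a limited form. The comparison stated for Trials 2 and 3 has about 33–37% power for the article's own minimum difference, against about 78–80% for an analysis of the same students by concordance with the PTR. The article gives no power for these trials, and 500 per arm in the abstract contradicts 25%/75% of 1000.

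The size rests on unadjusted binary remission, on a randomized mean of 22.5% or 24.2%, and on the estimated PTR attaining the full 5 points. The last is a best case: the simulation defines optimized treatment as each student receiving what is truly better for them, and an estimated rule may deliver less. It would therefore be wrong to infer that the concordance analysis guarantees 80%. Covariate adjustment could raise both powers somewhat; a smaller gain or more loss lowers both. The advantage in precision does not depend on the full gain being reached. Allocation and data collection are not compromised, so this can be corrected in the analysis specification.

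**What to change.** 1. Compute the PTR recommendation for all 1000 students in each later trial from their baseline data, and store it, including for the 750 who are randomized.
2. Make the primary Trial 2 and 3 estimator of PTR minus balanced randomization use all students with the known assignment probabilities (1/2 for the recommended arm, 1/4 for each other arm). That is (2/3) × (concordant mean − discordant mean), with covariate-adjusted IPW or TMLE. This targets the contrast already defined in the section on heterogeneity of treatment effects.
3. Correct the abstract from 500 per arm to 250 and 750.
4. State the power of the chosen analysis for 5 points, with its assumptions on the gain attained and on loss to follow-up. Say that the 500-per-arm simulation refers to model building in Trial 1.

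The cost is some extra analysis work and a less favourable stated power for the simple group comparison. No additional students and no change to the allocation are needed.
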